### **Statistical analysis**

Results are presented as mean  $\pm$  standard deviation. We will compare the results of infants treated with insulin to those receiving standard care on an intention to treat basis and within each group we will also compare the results of SGA infants to AGA infants.

Comparison between the groups on all different time points will be analysed using the unpaired t-test.

Within group differences between different time points and differences between the groups in the changes of the values in time will be analysed with repeated measures analysis of variance (ANOVA).

A p value of  $<0.05$  will be considered as statistically significant

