## Abbreviations

|       |                                            |
|-------|--------------------------------------------|
| ACTH  | adrenocorticotrophic hormone               |
| AGA   | appropriate for gestational age            |
| CRH   | corticotrophin releasing hormone           |
| DEXA  | dual energy x-ray absorptiometry           |
| FSH   | follicle stimulating hormone               |
| GA    | gestational age                            |
| GH    | growth hormone                             |
| GH-BP | GH-binding protein                         |
| HPA   | hypothalamic-pituitary-adrenal             |
| HPG   | hypothalamic-pituitary-gonadal             |
| IGF   | insulin-like growth factor                 |
| IGFBP | insulin-like growth factor-binding protein |
| IUGR  | intrauterine growth retardation            |
| LBW   | low birth weight                           |
| LH    | luteinizing hormone                        |
| SGA   | small for gestational age                  |
| SDS   | standard deviation score                   |
| VLBW  | very low birth weight                      |

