closely related to the duration of gestation. Bolt et al. showed that AGA preterms born < 30 weeks of gestation had a lower response of cortisol to ACTH stimulation on the 5th to 10th day of life compared to AGA preterms born between 30 and 33 weeks [32]. In preterm infants birth weight SD score as a measure for intrauterine growth was positively associated with the cortisol response to ACTH stimulation [33]. The lower adrenal response to stimulation may be involved in the higher risk of neonatal morbidity in very preterm infants, and especially in growth restricted preterm infants. In agreement with this, Scott et al. found that plasma cortisol levels in preterm infants not only significantly correlated with gestational age but also with markers of illness [34].

In conclusion, prematurity and fetal growth restriction have consequences for the function of the HPA-axis in the neonatal period and this is probably associated with neonatal morbidity.

With respect to morbidity in adult life one of the proposed mechanisms underlying the associations between intrauterine growth restriction and adult cardiovascular disease and its risk factors (hypertension, insulin resistance) is intrauterine programming of the HPA-axis. Phillips et al. found an inverse relation between birth weight and fasting plasma cortisol in adults. These cortisol concentrations correlated positively to systolic blood pressure, fasting and 2-hour plasma glucose concentrations after an oral glucose tolerance test, plasma triglyceride levels and insulin resistance [35,36]. Even in prepubertal SGA children born at term compared to AGA children born at term salivary cortisol concentrations during the day were higher, and therefore indicative of increased HPA-activity [37].

Case control studies comparing small for gestational age to normal birth weight children born at term show that in contrast to the low DHEAS levels at birth, DHEAS levels are higher than average in older low-birth weight children [10,13,38,39]. Recently, a large birth cohort study of unselected UK subjects (ALSPAC) showed a rather continuous inverse relationship between birth weight and DHEAS levels throughout the range of birth weights [40], comparable to the relationships between birth weight and disease risk in adulthood [41].

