#### Inclusion criteria:

- birth weight < 1500g
- less than 24 hours of age
- requiring intensive care and in whom it is considered appropriate to continue intensive care
- written informed parental consent

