### Objectives

#### Primary:

1. Growth and catch up growth and body composition during the first two years corrected age

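### The planned SGA-versus-AGA comparison within each arm mixes growth restriction with maturity, because entry is limited by birth weight alone, and it cannot show whether insulin acts differently in SGA infants

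*Protocol*

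**What the plan says.** The Statistical analysis section first plans insulin against standard care by intention to treat, then adds that "within each group we will also compare the results of SGA infants to AGA infants". Two methods follow. "Comparison between the groups on all different time points will be analysed using the unpaired t-test", and changes over time go to repeated measures ANOVA, with p<0.05 as the threshold. Neither method carries a gestational-age covariate, stratum or matching, and no arm-by-SGA term is written.

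The inclusion criteria limit size with "birth weight < 1500g". Neither the inclusion nor the exclusion list limits gestational age. SGA is expanded in the Abbreviations as "small for gestational age", but no centile, SDS cut-off or reference chart is given.

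The primary objective is "Growth and catch up growth and body composition during the first two years corrected age". No listed question or objective asks about SGA infants, or whether insulin acts differently in them.

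**The concern.** There are two difficulties.

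First, a birth-weight ceiling without a gestational-age limit selects on a joint function of maturity and growth. At gestations where nearly every infant weighs less than 1500 g, both SGA and AGA infants enter. At gestations where the typical infant weighs more, those who enter are mostly the small ones. SGA status among the enrolled therefore goes with greater maturity, even if the two were unrelated among all births. An unadjusted SGA-AGA difference is then not an estimate of the effect of growth restriction.

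Second, splitting the comparison by arm invites a reader to set the two p-values side by side. A difference seen in controls and not in insulin-treated infants could be taken as insulin removing a disadvantage of SGA infants. Two separate tests do not support that inference; only the difference between the two contrasts addresses it.

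**Working it through.** **Plan's own figure.** The protocol gives no number for the SGA/AGA comparison or for an interaction. Its 30 evaluable infants per arm were chosen for insulin against control and are used here only as an input. (That figure for 0.5 SDS at 80% power, two-sided, reproduces only if the SD is about 0.68 to 0.69 SDS. This is a separate matter on which nothing below depends.)

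**1. Direction of the maturity gap.** Take one gestation, 32 weeks. Assume normally distributed birth weight with median *m* and coefficient of variation *c*, and SGA meaning below the 10th centile. These are assumptions, as the protocol supplies no chart.

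- Probability of entry: P = Φ((1500 − m)/(c·m)).
- Share of entrants who are SGA: 0.10/P, capped at 1.
- m = 1750 g, c = 15%: z = −250/262.5 = −0.952, P = 0.170, SGA share 0.10/0.170 = 59%.
- m = 1650 g, c = 18%: z = −150/297 = −0.505, P = 0.307, share 33%.
- m = 1850 g, c = 12%: z = −350/222 = −1.577, P = 0.057, which is below 0.10, so every entrant is SGA.

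At gestations where almost all infants weigh under 1500 g, P is close to 1 and the share stays at 10%. The proportion of SGA infants among those enrolled therefore rises with gestation.

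**2. Size of the gap.** A Monte Carlo of birth weight by gestational age, with SGA independent of gestational age before the limit, was run over 36 scenarios: CV 12, 15 or 18%; median weight at 32 weeks 1650, 1750 or 1850 g; two gestational-age mixes; SGA below the 10th centile or below −2 SD.

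| Population | SGA minus AGA, mean gestational age |
|---|---|
| No birth-weight limit | about 0 weeks |
| Birth weight < 1500 g | 1.2 to 2.6 weeks |
| Birth weight < 1500 g and gestation capped at 32 weeks | 0.8 to 1.6 weeks |

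Other assumed curves put the lower end at 0.9 to 1.0 week without the cap. About 1 to 2.5 weeks is a fair summary.

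**3. Which outcomes are exposed.** IGFBP-3 in blood, and FSH, LH, oestrogens and androgens in urine, are taken on postnatal days 7 and 28. At those visits the SGA and AGA groups differ in maturity by the full gap. The Rationale reports low IGFBP-3 both in extremely preterm infants and in SGA infants born at term, so both factors bear on that outcome. Most anthropometry, and the neurodevelopmental tests, are at postmenstrual or corrected ages. This aligns maturity at the visit, but infants born earlier have then lived longer outside the womb and keep any morbidity tied to immaturity.

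**4. What two within-arm tests can show.** The SGA share is borrowed from the cohort cited under Sample size consideration: 15/(15+26) = 37%, and 30 × 15/41 = 11 SGA, leaving 19 AGA per arm. Effects are in SD units, with a two-sided 5% test.

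- SE within an arm: √(1/11 + 1/19) = 0.379.
- Power in one arm, p, by noncentral t on 28 df: 24.7% at 0.5 SD, 48.1% at 0.75, 72.2% at 1.0. The difference detectable with 80% power is 1.10 SD.
- With the same true difference in both arms (no interaction), the chance that exactly one arm reaches p<0.05 is 2p(1 − p):

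| True SGA-AGA difference, both arms | p | 2p(1 − p) |
|---|---|---|
| 0.5 SD | 0.247 | 37% |
| 0.75 SD | 0.481 | 50% |
| 1.0 SD | 0.722 | 40% |

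**5. What an interaction could show.** SE = √(2 × (1/11 + 1/19)) = 0.536. Multiplied by 2.8, this gives 1.50 SD detectable with 80% power (1.53 by noncentral t). The main treatment effect has SE √(2/30) = 0.258, so the interaction is 0.536/0.258 = 2.1 times less precise. Splits of 15/15 and 6/24 per arm give 1.47 and 1.84 SD by noncentral t. Power for an interaction of 0.5 SD is 12 to 16% across the three splits.

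**The case against.** The strongest reply is that the protocol sets no aim that this analysis fails. None of its questions or objectives concerns SGA infants, and the sentence only says that they will also be compared. A reader might infer that the within-arm tests are meant to show a differential insulin effect. The text does not say so, and the point here is only that they could not.

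A reader might also take the Rationale's statement that adrenal cortex function is "closely related to the duration of gestation", or that "plasma cortisol levels in preterm infants not only significantly correlated with gestational age but also with markers of illness", as proof that the adrenal results will be biased. That goes too far. Those statements concern the neonatal period, while this study measures DHEAS at 6 and 24 months and salivary cortisol at 24 months corrected age. Nothing in the protocol shows gestational age driving those later values.

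Nor are SGA infants necessarily more mature. The gap is an average, and its size depends on curves that the protocol does not supply. The requirement for intensive care may keep out some of the more mature small infants; the 32-week cap in the working gives a rough idea of how far the gap could then shrink, and it does not vanish. Corrected-age visits, and a growth target stated in SDS, already remove part of the problem.

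Finally, the t-test sentence speaks of comparison between the groups, a word that otherwise denotes the arms. Applying it to SGA against AGA is the natural reading, as no other test is offered, but it is a reading. A statistical analysis plan, which was not available, could add adjustment.

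These replies narrow the point. They do not supply an adjustment that the protocol leaves out, and they do not make two within-arm p-values a test of effect modification.

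**Conclusion.** The point holds in a limited form. Followed as written, the plan gives an SGA-AGA contrast in each arm that mixes growth restriction with a maturity difference averaging about 1 to 2.5 weeks. The direction follows from the entry criterion; the size rests on the assumed growth curve, its spread, the gestational-age mix and the SGA cut-off. The exposure is clearest on days 7 and 28 and weaker at corrected-age visits. No bias on any particular outcome has been quantified, so it cannot be said that an effect would be masked or reversed.

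A result significant in one arm only would be weak evidence of anything. It arises 37 to 50% of the time with equal true differences of 0.5 to 1.0 SD, given the assumed 11 and 19 per arm. That split is borrowed from another cohort. In the simulations, a 10th-centile definition gives an SGA share of only 14 to 20%, about 4 to 6 infants per arm.

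A reader might infer that the trial's main comparison is compromised. It is not: insulin against control is randomised and unaffected. Severity is minor to moderate, since the analysis is secondary.

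**What to change.** Replace the within-arm SGA/AGA tests with one model per outcome over both arms, containing treatment, birth-weight SDS (or SGA status) and gestational age. Name the birth-weight reference chart, and define SGA if the category is kept. Continuous SDS avoids dependence on a cut-off and uses all 60 infants for the growth-restriction question.

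If a differential insulin effect is of interest, add a treatment-by-birth-weight-SDS interaction, report it with its confidence interval and label it exploratory. For an SGA-against-AGA contrast, only a difference of about 1.5 SD would be detectable at this size. Keep SGA/AGA tables by arm as description, without p-values.

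The cost is a change of analysis wording; the variables are known at birth. The within-arm p-values are given up. At higher gestations there is little overlap, because few AGA infants weigh under 1500 g, so the adjusted estimate there leans on the model and will be less precise. The report should show the distribution of gestational age by SGA status.

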## **Sample size consideration**

Bolt et al [56] studied growth and body composition in 15 SGA and 26 AGA preterm born infants during the first 2 years of life. They found that growth expressed as anthropometry according to Dauncey [57], IGF-1 and IGFBP-3 were significantly lower in SGA than in AGA infants ( $p < 0.01$ ). Catch up growth during the first year of life was significantly higher in SGA infants compared to AGA infants ( $p < 0.01$ ).

In addition, growth and body composition was studied in 14 preterm infants with chronic lung disease and treated with corticosteroids to facilitate weaning from

the ventilator and 18 preterm controls during the first 2 years of life [58]. Body composition at term and 3 months corrected age in preterm infants treated with dexamethasone for chronic lung disease, who received extra caloric intake until term age, did not differ from preterm infants without CLD.

Based on the results of both studies in combination with power calculation it is expected that groups of 30 fully evaluable subjects (insulin treated vs. controls) will be sufficient to detect a difference of 0.5 SDS in growth parameters with a power of 80% at  $\alpha=0.05$ .

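### The between-arm t-test at each visit leaves SGA/AGA status unadjusted, a modest and avoidable loss of efficiency: about 6 points of power if the protocol's cited p<0.01 reflects the true strength of the association

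*Protocol*

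**What the plan says.** Under Statistical analysis, the insulin and control arms are compared visit by visit: "Comparison between the groups on all different time points will be analysed using the unpaired t-test". The analysis is by intention to treat, and no covariate is named. Changes over time are compared between arms by repeated measures ANOVA, also without covariates.

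SGA/AGA status enters the analysis in one place only: "within each group we will also compare the results of SGA infants to AGA infants". That contrast lies inside each arm and removes no variance from the treatment comparison.

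The Sample size consideration cites a cohort of 15 SGA and 26 AGA preterm infants followed for two years. Anthropometric growth was lower in the SGA infants, and "IGF-1 and IGFBP-3 were significantly lower in SGA than in AGA infants" (p<0.01). Catch-up growth in the first year was higher in the SGA infants (p<0.01). The section then concludes that "groups of 30 fully evaluable subjects (insulin treated vs. controls) will be sufficient" for a difference of 0.5 SDS at 80% power and α=0.05.

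**The concern.** Growth is part of the primary objective, and the t-test is a method the protocol commits to. SGA status is fixed at birth, cannot be affected by treatment, and is available for every infant because the plan groups by it. The protocol's own evidence links it to growth, IGF-1 and IGFBP-3. Leaving it out of the treatment comparison puts explainable variation into the error term.

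With 60 infants in total and no dropout allowance stated, precision is scarce. A covariate named in advance is also easier to defend than one added after the results are known.

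**Working it through.** **Inputs.** From the Sample size consideration: n = 30 per arm, difference 0.5 SDS, power 80%, α 0.05; cited cohort 15 SGA and 26 AGA, p<0.01. Assumed, because the protocol does not state them: a two-sided test, the SD of the growth SDS, and the SGA share in this trial.

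**1. The plan's own power figure.** For the unpaired t-test the noncentrality is (0.5/SD)·√(30/2) = (0.5/SD)·3.873 on 58 df.
- SD = 1.0: noncentrality 1.936, power 47.8%. The stated 80% is not reproduced.
- Power of 80% needs a standardised difference of 0.736, so SD = 0.5/0.736 = 0.68.

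Both are used as starting points below.

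**2. Strength of the SGA association.** If the cited p-value came from a two-group t-test, p<0.01 requires |t| ≥ 2.708 on 39 df:
- R² = t²/(t²+39) = 7.333/46.333 = 0.158
- standardised difference = 2.708·√(1/15+1/26) = 0.878

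This is a floor for the observed value in 41 infants. A smaller p would raise it (p = 0.001 gives 0.245). Selection by significance in a small study would make it too high as an estimate of the truth (0.137 after the usual adjustment of R² for degrees of freedom).

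**3. Power after adjusting for SGA status.** Adjustment divides the residual variance by 1/(1−R²) and costs one degree of freedom. It also inflates the variance of the treatment effect for chance imbalance in the covariate, by 1/(1−r²), where r² is the squared correlation between arm and SGA status. Its expected value is 1/(60−1) = 0.017. So the noncentrality is multiplied by √(0.983/(1−R²)), on 57 df. The table averages over binomial SGA counts with a share of 15/41 = 0.366.

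| R² | Multiplier | Power, SD 1.0 (base 47.8%) | Power, SD 0.68 (base 80.0%) |
|---|---|---|---|
| 0 | 0.991 | 47.1% (−0.7) | 79.3% (−0.7) |
| 0.05 | 1.017 | 49.1% (+1.3) | 81.3% (+1.3) |
| 0.10 | 1.045 | 51.2% (+3.4) | 83.3% (+3.3) |
| 0.158 | 1.080 | 53.9% (+6.1) | 85.7% (+5.7) |
| 0.25 | 1.145 | 58.7% (+10.9) | 89.3% (+9.3) |

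Counting only the lost degree of freedom gives 54.6% and 86.3% at R² = 0.158, which is slightly too favourable.

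**4. Dependence on the SGA share q.** Holding the SGA difference at 0.878 within-group SD, R² = q(1−q)·0.771/(1+q(1−q)·0.771).
- q = 0.10: R² = 0.065, gain about 2 points
- q = 0.20: R² = 0.110, gain about 4 points
- q = 0.366: R² = 0.152, gain about 5.5 to 6 points
- q = 0.50: R² = 0.162, gain about 6 points

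**5. Is chance imbalance a separate harm?** In within-group SD units:
- variance of the between-arm gap in SGA share: 2·0.366·0.634/30 = 0.0155
- its contribution to the variance of the mean difference: 0.0155·0.771 = 0.0119
- total variance of the mean difference: (1+0.179)·2/30 = 0.0786
- ratio: 0.0119/0.0786 = 0.152

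The ratio is the R² of step 4. Imbalance is therefore the same lost efficiency seen from another side, already inside the t-test's standard error.

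**The case against.** The strongest reply is that this is a preference about efficiency. Under randomisation the t-test is unbiased with correct type I error, and covariates are often settled in a SAP, which is not at hand. The first part stands. The second stands only in part, because the protocol does name the between-arm test.

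Other limits also stand:
- The p<0.01 is reported for several measures over two years, with no visit, test or effect size. Because SGA infants also caught up faster, the association may weaken with age, so one R² cannot be assumed at every visit.
- The Rationale reports no SGA/AGA difference in body composition relative to body weight in the first year, and body composition shares the primary objective with growth.
- The repeated measures ANOVA removes stable differences between infants when change is compared. It does not help the comparison of levels at a visit.

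A reader might infer that gestational age should be adjusted for on the same grounds. The protocol gives no evidence that it predicts growth, and visits from 32 weeks onward are already timed by postmenstrual or corrected age. A reader might also extend the point to adrenal outcomes, since "In preterm infants birth weight SD score as a measure for intrauterine growth was positively associated with the cortisol response to ACTH stimulation". That concerns a neonatal stimulation test; this study measures salivary cortisol at 24 months and DHEAS at 6 and 24 months.

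Nor does the absence of a described stratification show that there was none: randomisation belongs to the parent trial, which is only summarised here.

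**Conclusion.** The point holds as a modest loss of efficiency in the treatment comparison at each visit, for growth, IGF-1 and IGFBP-3. Its size is about 6 points of power at 30 per arm if R² is about 0.16 and the SGA share about 37%. Across an R² of 0.05 to 0.25 it is about 1 to 11 points, and it is smaller if fewer infants are SGA.

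Three stronger readings are not supported. The t-test is neither biased nor invalid. A chance excess of SGA infants in one arm is not a second harm on top of the lost power. And the protocol does not show that SGA status strongly predicts the outcomes or that a fixed amount of power is lost, because it reports only a significance threshold from 41 infants.

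That the stated 80% needs an SD of about 0.68 is a separate and larger matter. From an SD of 1.0, this adjustment recovers power only to about 54%.

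**What to change.** Replace the sentence on the unpaired t-test under Statistical analysis with:

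> *At each time point the groups will be compared by a linear model (ANCOVA) with treatment group and SGA/AGA status (or birth weight SDS) as covariate. The adjusted mean difference with 95% CI is the main comparison for growth, IGF-1 and IGFBP-3; the unpaired t-test is a sensitivity analysis.*

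Gestational age at birth is optional. If it is wanted, name it in advance too.

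**Cost.** One sentence, with no new data, visits or patients. Results become adjusted rather than raw differences. If SGA status proves not prognostic, power falls by about 1 point (0.7 in the table), or by about 1.5 points with two useless covariates.

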## 2. Insulin sensitivity

- fasting glucose and insulin in plasma and calculation of insulin sensitivity using the HOMA method [60] at the corrected age of 6 and 24 months

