## 5. Gonadotrophins and steroids

- gonadotrophin (FSH and LH) measurements in urine on day 7 and 28, at 32 weeks postmenstrual age, at expected date of delivery (40 weeks) and at the corrected age of three months. As shown by Kuijper et al. urinary gonadotrophin levels are a proper reflection of the serum levels [61].
- oestrogens and androgens in urine on day 7 and 28, at 32 weeks postmenstrual age, at expected date of delivery (40 weeks) and at the corrected age of three months

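### The protocol prescribes a raw-scale t-test without sex for hormone and HOMA outcomes, which may cost power, and leaves undefined how many infants enter each sex-steroid comparison

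*Protocol*

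**What the plan says.** The Statistical analysis section of the protocol gives a single rule. The summary is fixed ("Results are presented as mean" and standard deviation), and so is the between-arm test: "Comparison between the groups on all different time points will be analysed using the unpaired t-test". Repeated measures ANOVA is added for within-group change and for differences between arms in change over time. The only other factor named is size at birth: "within each group we will also compare the results of SGA infants to AGA infants". Sex, a log scale, geometric means and rank methods do not appear.

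The outcomes under this rule include "gonadotrophin (FSH and LH) measurements in urine on day 7 and 28" and at later visits, "oestrogens and androgens in urine on day 7 and 28" and at later visits, DHEAS and salivary cortisol, and "fasting glucose and insulin in plasma and calculation of insulin sensitivity using the HOMA method". The Objectives section lists HPG development, insulin sensitivity and adrenal function as secondary; the Questions section places the same topics under primary questions.

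On the steroids, sections 5 (Gonadotrophins and steroids) and Urine sample analysis both say that oestrogens and androgens are measured in urine. The Measurements table in the appendix instead lists *E or A* at each of the five urine time points. The protocol does not say which infants get which assay.

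**The concern.** Hormone concentrations and HOMA take only positive values, and HOMA is built from a product of insulin and glucose. If such values are right-skewed, a few high readings dominate a raw mean and widen its standard error. If the level of a hormone depends on sex, leaving sex out puts the boy-girl gap into the error term. With only 30 infants per arm there is little precision to spare, and a null result on the HPG objective could reflect the chosen analysis rather than the absence of an effect.

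The mismatch on steroids raises a further question that needs no assumption about biology: the number of infants contributing to an oestrogen or an androgen comparison cannot be read from the protocol.

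**Working it through.** **The plan's own figure.** Sample size consideration states that 30 evaluable infants per arm detect 0.5 SDS in growth parameters with 80% power at alpha 0.05. No power or precision is stated for any hormone or for HOMA, so there is no figure to reproduce for these outcomes. For orientation only: with an SD of 1 and a two-sided t-test, 30 per arm gives 48% power for 0.5 SD, and 80% power needs a difference of 0.736 SD. The growth calculation is a separate matter. Here 0.736 serves only as a benchmark, the effect that has 80% power when scale and sex are handled well.

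**Inputs.** From the protocol: 30 per arm, alpha 0.05, unpaired t-test. Assumed: two-sided testing, an equal mix of boys and girls, the size of the sex gap, and the log-SD.

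**Step 1: leaving sex out.** With a gap of g within-sex SDs and a 50:50 mix, the pooled variance is multiplied by 1 + g²/4, and the standardised effect becomes 0.736/√(1 + g²/4).
- g = 1: 1 + 1/4 = 1.25; effect 0.658; power 71%; 60 infants are worth 60/1.25 = 48.
- g = 2: 1 + 4/4 = 2.0; effect 0.520; power 51%; worth 30.
- g = 3: 1 + 9/4 = 3.25; effect 0.408; power 34%; worth about 18.

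**Step 2: raw instead of log scale, no sex gap.** Simulated log-normal data, 30 per arm, ratio of geometric means exp(0.736 × log-SD). The log-scale t-test has 80% power throughout. The raw-scale t-test has:
- log-SD 0.3: 78%
- log-SD 0.5: 75%
- log-SD 0.6: 73%
- log-SD 1.0: 61%

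**Step 3: both together.** At log-SD 0.5 with a two-fold sex ratio, power is 57% for the raw t-test, 63% for the log t-test without sex, and 80% for the log model with sex. At a three-fold ratio the figures are 43%, 47% and 80%.

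**Step 4: type I error.** Over log-SDs of 0.3 to 1.0 and sex ratios of 1 to 10, the raw t-test rejects a true null in 3.6% to 5.1% of simulated trials. It is not inflated.

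**Step 5: the steroid assays.** Side by side, two sections of text have both steroids measured, and the table has one or the other. If both are assayed in every infant, each comparison has 30 per arm. If one is assayed per infant according to sex (an assumption), each has about 30/2 = 15 per arm. Power for 0.5 SD is then 26%, against 48% at 30 per arm, and the difference detectable with 80% power is 1.06 SD instead of 0.736 SD.

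**The case against.** The strongest reply is that the premises are not in the protocol. It reports no SD, skewness, observed range or boy-girl difference for any of these analytes in infants. That stands: every power figure for sex and scale is conditional.

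A reader might look to the assay sheet, where the coefficient of variation for insulin is nearly constant over a wide range, as proof that a log scale is needed. It is not. Those figures describe laboratory error, not spread between infants. The sheet itself warns that the coefficient depends on sample and concentration, and for salivary cortisol it falls from 19% to 7%. Nor do the assay ranges show that infants' values span orders of magnitude.

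A reader might also infer that chance sex imbalance between the arms would pass for a treatment effect. Under randomisation the t-test's standard error already allows for this, as step 4 shows.

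The repeated-measures comparison of change is a fair counterweight: a sex difference that is constant on the analysed scale cancels within each infant, so step 1 applies only to the comparisons at single time points. Those comparisons remain planned, however. The first amendment urine sample is on day 7, so a treatment effect already present then and maintained would cancel from the change as well.

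Pooling of boys and girls is inferred from silence. If *E or A* means assignment by sex, the two steroids are not pooled and step 1 does not apply to them.

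Finally, a statistical analysis plan could add a transformation and covariates. But the protocol is not silent here. It names the summary and the test for all outcomes, and a plan that followed it would use the raw scale without sex.

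**Conclusion.** The point holds in a conditional form. The protocol commits every hormone and HOMA outcome to raw-scale means and t-tests without sex. For LH and FSH, a sex gap of 1 to 3 within-sex SDs would cut power at single time points from 80% to between 71% and 34%. The choice of scale costs about 2 points of power at log-SD 0.3, 7 at 0.6 and 19 at 1.0.

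For HOMA only the scale argument applies, because nothing in the protocol suggests a sex difference. A claim that the insulin-sensitivity comparison loses much of its precision would go too far: the loss is modest unless the log-SD is near 1.

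The consequence throughout is lost precision. There is no bias and no excess of false positives.

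The disagreement over the steroid assays rests on the text alone. Until it is resolved, the size of each steroid comparison is undefined. The figure of 15 per arm is one possible reading, not an established fact.

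**What to change.** In Statistical analysis, state that the positive-valued hormone and HOMA outcomes are analysed on the log scale and reported as geometric means and between-arm ratios with 95% confidence intervals. For the HPG outcomes, include sex as a factor in the between-arm comparison and show the results by sex.

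Reconcile section 5 and Urine sample analysis with the Measurements table: say whether each sample is assayed for both steroids or for one and, if one, by what rule. If the rule is sex, state that each steroid comparison is within one sex with about 15 per arm, and give the detectable difference.

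The cost is a few sentences. Sex is a known baseline value and uses one degree of freedom, and the analysis change needs no new sample or visit. Readers will see ratios instead of raw differences. If skew and sex gap turn out small, almost nothing is lost: with no sex gap, the simulated log model with sex kept about 79% power against 80% without it.
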